### Data management and analysis

All participants will be allocated a participant identification number (PID) code at enrolment, which will be used on samples and documents over the 12-month study period. Data will be downloaded to a secure server and kept in a password-protected system. Laboratory results will be merged into the main dataset using the unique PID.

Data will be entered into SPSS V.24 and the analyses conducted using STATA V.15. The socio-demographic and clinical characteristics of participants will be summarised using means and SD continuous variables. For categorical variables, proportion (%) will be reported. Significant associations in contingency tables (cross tabulations) will be assessed using the standard Pearson’s χ^2^ test. An independent samples t-test will be used for comparing differences in continuous variables between two groups. If there are more than three groups, we will use ANOVA methods. A p value less than 0.05 will be regarded as statistically significant. In addition, we may also apply growth mixture modelling to observe whether subsets of individuals follow distinct trajectories over time.

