### Socio-demographic profile of PLWHIV and first episode psychosis

There is limited literature on the association of HIV and FEP, with previous studies mainly describing HIV prevalence rates or clinical profiles.^8^ A Ugandan study by Lundberg and colleagues^9^ found that HIV-positive patients with mental illness were more likely to be women and older (40–49 years). A KwaZulu-Natal (KZN) Province, SA, study of patients with FEP reported a higher HIV prevalence in less educated individuals; however, this was a small sample.^8^ In a more recent chart review of patients with psychosis admitted to a psychiatric hospital in SA, HIV-infected patients with psychotic disorders were more likely to be women (74.0%), younger than 50 years (94.0%) and less likely to have secondary education than HIV-negative patients with psychotic disorders (56.0% vs 72.0%).^10^

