### PLWHIV and FEP and substance use

Studies traditionally suggest an association between substance use in FEP patients and HIV infection.^1^ Substance use patterns vary across the different regions of SA. This may be related to both ethnic and socioeconomic differences.^14^ Davis *et al* confirmed both the growing pattern of substance use as well as the trend of psychiatric comorbidity in KwaZulu-Natal (KZN). The rates of substance use in this province were also significantly higher than that reported in studies of the general population in SA.^14^ Another study of patients with FEP in KZN, SA, reported lower rates of self-reported substance use among HIV-positive than HIV-negative patients with mental illness,^8^ which was further supported by a retrospective chart review of patients with psychosis.^10^ This may suggest that either substance use/misuse may not be a significant factor in HIV transmission in the KZN context, or that the study results were limited by under-reporting or the small sample size. Thus, while the international literature suggests that PLWHIV and mental illness may be vulnerable to substance use, this has not been borne out in the local KZN studies and warrants further research.

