### Participant selection and sampling strategy

All adult inpatients or outpatients with FEP meeting the inclusion criteria will be recruited to the study over a 3-year period. The sample size calculation was based on a log-rank test group. In order to achieve an 80% power to detect an OR of 1.857 (to maximise variability), in a design with three repeated measurements having a compound symmetry covariance structure when the proportion from group 2 is 0.500, the correlation between observations on the same subject is 0.500, and the alpha (significance) level 0.05 or 5%, a sample of 130 PLWHIV and FEP and 130 HIV negative with FEP will be required. In addition, this sample size accounts for and permits a 10% dropout rate over an anticipated 36-month accrual with a minimum follow-up of 12 months.

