### Study significance

We postulate that the course and outcome of HIV psychosis differs from that in an HIV-negative individual, and that this study may provide valuable insight into the impact of HIV infection on psychosis presentation and outcomes. Longitudinal comparative cohort studies of this nature are limited and have not been conducted locally in one of the highest HIV prevalence settings in Africa, hence the data will serve to introduce new knowledge on the topic, as well as form the baseline for future research and treatment. A clearer understanding of the association between HIV and psychosis may provide better insight into HIV as a neurotropic virus. The findings of this study will contribute towards improving the care and management of patients with FEP and HIV.

WHO reports that in 2020, psychiatric conditions are ranked the second leading cause of global disease burden after ischaemic heart disease.^47^ In the South African context, this is even more pronounced by the additional burden of HIV infection and AIDS. With an approximate overall HIV prevalence rate of 11.2% (6.19 million) and an estimated 16.6% of the population (adults aged 15–49 years) being HIV positive, SA is in urgent need of interventions to address the related adverse consequences. Psychotic disorders are associated with a significant burden of disease and often use the limited mental health resources. Understanding the association between HIV and psychosis in the era of antiretroviral treatment is thus an urgent priority. Using the HIV psychosis as a potential model for schizophrenia may also improve our understanding of its neurobiology. The new knowledge, generated through this novel study, will enable an understanding of the interplay between HIV and psychosis at a fundamental level, centred at the international epicentre of the HIV pandemic.

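### The cognition, course and 12-month comparisons are to be read as HIV effects, but the only group tests named are unadjusted, although the protocol cites sex and education imbalances in earlier cohorts

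*Protocol article*

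**What the plan says.** All of the following is in the Protocol article.

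- **Named tests** (Data management and analysis). For categorical variables: "Significant associations in contingency tables (cross tabulations) will be assessed using the standard" Pearson χ² test. For continuous variables: "An independent samples t-test will be used for comparing differences in continuous variables between two groups". ANOVA is given for larger numbers of groups, with p < 0.05 as the threshold. Beyond these, "we may also apply growth mixture modelling to observe whether subsets of individuals follow distinct trajectories over time".
- **How the groups arise** (Participant selection and sampling strategy). All eligible patients are recruited and HIV status defines the groups. Neither matching nor stratification is mentioned.
- **Expected differences.** The Abstract hypothesises that the two groups will be distinct socio-demographically as well as clinically and cognitively. The section on socio-demographic profile cites a South African chart review in which HIV-infected patients with psychosis were "more likely to be women (74.0%), younger than 50 years (94.0%) and less likely to have secondary education than HIV-negative patients"; the education figures are 56.0% and 72.0%. The substance use section cites a local study that "reported lower rates of self-reported substance use among HIV-positive than HIV-negative patients with mental illness".
- **Intended reading** (Study significance). The authors expect that "this study may provide valuable insight into the impact of HIV infection on psychosis presentation and outcomes". The same section later speaks of learning what HIV contributes to psychosis onset, and of management algorithms and policy change.
- **Limitations** (Methodological challenges and study limitations). Confounding is not listed.

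**The concern.** HIV status is not assigned, so a crude difference between the groups mixes any effect of HIV with everything else on which the groups differ. Sex and schooling plausibly affect neuropsychological scores, symptoms and quality of life. If the HIV-positive group has less schooling, it may score worse on the cognitive battery for that reason alone, and a t-test cannot separate the two.

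Growth mixture modelling does not fill the gap. It is optional, it looks for subgroups with different trajectories, and it is not described as giving an adjusted HIV contrast.

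At stake is whether the study's main longitudinal conclusions can be attributed to HIV at all.

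**Working it through.** **1. The plan's own figure.** The stated size is 130 per group, for 80% power, OR 1.857, reference proportion 0.50, three measurements, correlation 0.5, alpha 0.05 and 10% dropout.

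- p1 = 1.857 × 0.5 / (0.5 + 1.857 × 0.5) = 0.650.
- Two-sided comparison of 0.650 with 0.500 without continuity correction: 170 per group.
- Compound-symmetry factor: (1 + 2 × 0.5)/3 = 0.667, giving 114.
- Dropout: 114/0.9 = 127, against 130 stated.

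The size reproduces within 3% and is not at issue here. Completers per group are 130 × 0.9 = 117, which is used below.

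**2. Inputs for the bias check**

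| Input | Value | Source |
|---|---|---|
| Without secondary education, HIV+ vs HIV− | 44% vs 28% (100 − 56, 100 − 72) | Cited chart review |
| Women, HIV+ | 74% | Cited chart review |
| Women, HIV− | 30–50% (40–60% in step 5) | Assumption; not in the document |
| Confounder–outcome strength | OR 1.5–3, or 0.3–0.8 SD | Assumption; not in the document |
| Outcome risk, HIV− | 0.50 | Reference proportion in the sample size section |
| True HIV effect | none | Null, to isolate confounding |

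**3. Education alone, binary outcome, one time point.** Let b be the risk without the confounder and e = OR·b/(1 − b + OR·b) the risk with it. Group risk = share × e + (1 − share) × b, with b set so that the HIV− risk is 0.50.

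For OR 2: b = 0.452 and e = 0.623.

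- HIV+ risk = 0.44 × 0.623 + 0.56 × 0.452 = 0.527.
- Difference = 0.027; SE = √(0.527 × 0.473/117 + 0.5 × 0.5/117) = 0.065; ratio = 0.42.
- Two-sided rejection rate = 7.0%.

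| Confounder OR | Crude OR with no HIV effect | Rejection rate (nominal 5%) |
|---|---|---|
| 1.5 | 1.07 | 5.7% |
| 2 | 1.12 | 7.0% |
| 3 | 1.19 | 9.9% |

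**4. Sex alone, same method, 74% women in HIV+**

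| Women in HIV− (assumed) | Confounder OR 1.5 | OR 2 | OR 3 |
|---|---|---|---|
| 50% | 1.10; 6.6% | 1.18; 9.7% | 1.30; 16.7% |
| 40% | 1.15; 8.2% | 1.26; 14.5% | 1.44; 28.8% |
| 30% | 1.20; 10.4% | 1.35; 21.2% | 1.61; 43.9% |

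Cells give the crude OR and the rejection rate.

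**5. Continuous outcome.** Bias = difference in share × effect in SD; SE = √(2/117) = 0.131.

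- Education alone: 0.16 × 0.3, 0.5, 0.8 SD = 0.048, 0.080, 0.128 SD, with rejection rates 6.6%, 9.4%, 16.5%.
- Sex and education together, independent, same direction, 0.3 SD each:
  - 60% women in HIV−: 0.048 + 0.14 × 0.3 = 0.09 SD, 10.6%.
  - 40% women in HIV−: 0.048 + 0.34 × 0.3 = 0.15 SD, 20.9%.

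**The case against.** **Crude comparison is right for part of the study.** This stands. The stated aim includes comparing the socio-demographic, substance use and trauma profiles, and the design is called descriptive. For that purpose sex, schooling and substance use are results in themselves. A reader might infer that every crude test in the plan is invalid; the document does not support that. The point is confined to cognition, course and 12-month outcome, where differences are to be attributed to HIV.

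**The article is condensed, and a full protocol or analysis plan may specify covariates.** This is partly fair: the list of tests is not said to be exhaustive, and the sample size assumes repeated measures that none of the named tests uses. But the article does not defer the choice. It names specific tests, and those cannot carry the stated interpretation.

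**The imbalances come from other cohorts.** This stands. A reader might infer that the protocol shows its own groups to differ, but it cites earlier studies. The chart review is not described as limited to first episodes. The substance use finding is hedged for under-reporting and small samples. The exclusion of patients with under 7 years of schooling may narrow the education gap, though differences above that level remain possible.

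**Age.** A reader might add age as a documented imbalance. The cited age findings concern patients aged 40–49 in one study and under 50 in another, and do not carry over to a cohort restricted to 18–45. Age belongs in the model on general grounds only.

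**The size is driven by assumptions.** This stands. The only imbalance documented for both groups is education, and alone it does little. A reader might quote a false-positive rate of a third or more; that needs strong assumed effects or an assumed sex mix that the document does not give. Lower substance use in the HIV-positive group could also bias the other way.

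**Conclusion.** The point holds for the cognition, course and 12-month outcome comparisons. Followed as written, the named tests would give confounded contrasts that the protocol intends to read as the impact of HIV.

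The size is modest to material. With no HIV effect, the error rate would be about 6–10% from the education gap alone (confounder OR 1.5–3), and about 10–21% from sex alone at OR 2 with 30–50% women among HIV-negative patients, against a nominal 5%. These rates rest on 117 completers per group, one time point, imbalances carried over from an earlier cohort, and assumed confounder strengths and HIV-negative sex mix. The direction is not fixed: biases may add, cancel or mask a true difference.

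This is a cheap improvement to the analysis, not a fault in the design or in the sample size.

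**What to change.** In Data management and analysis:

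- Estimate the HIV contrast for cognition, symptoms, quality of life and 12-month outcome from regression, using a mixed or GEE model where there are repeated measures. Adjust for age, sex, years of schooling and hospital. This would also match the correlated three-measurement design assumed for the sample size.
- Add a second model with substance use (ASSIST) and childhood trauma (CTQ), labelled as possible mediators or confounders, since their place in the causal order is uncertain.
- Use inpatient or outpatient status only in a sensitivity analysis. Admission may reflect severity of psychosis, which is itself an outcome.
- Keep the crude χ² and t-tests for the descriptive baseline profile, and label them so.
- List confounding among the limitations.

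Cost: a few degrees of freedom and a little more analysis work. ASSIST and CTQ are already in Table 1. Age and schooling must be established for eligibility, and the recruiting hospital is known. The article does not list the items of the socio-demographic questionnaire, so confirm that it records sex and years of schooling as such. No extra visits or participants are needed.

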### Patient and public involvement

No patients or members of the public were involved in the design, analysis or reporting of this current investigation.

### Ethics and dissemination

Ethical approval to conduct the study was obtained from the Biomedical Research Ethics Committee of the University of KwaZulu-Natal (UKZN). The study will be conducted in accordance with South African Department of Health Research Ethics guidelines (2015) as well as the UKZN policy on Research Ethics. Recruitment of study participants will commence as full ethics approval was received from Biomedical Research Ethics Committee. No other independent ethics review was required.

All participants fulfilling the inclusion criteria will be selected for the study, from whom written, informed consent will be obtained. All potential participants will have the opportunity to participate, which will be made known to them in the information sheet. Where participants are unable to consent independently, adequate steps will be taken to ensure that legally acceptable proxy consent is obtained. All participants testing HIV positive at any point in the study will be referred for ART and support.

The results from this investigation will be actively disseminated through peer-reviewed journal publications and conference presentations. On completion of the peer-review process, we will provide feedback to clinicians at Department of Health for further discussion about enhanced treatment algorithm.

## Discussion

### Potential risks

There will be minimal risk or discomfort to participants, with one test requiring bloods to be taken. The only active involvement of the participants is for them to provide verbal responses to assessment interviews and scales used for data collection. We acknowledge the potential risk of psychological distress to patients, as they may be directly affected by sensitive questions, for example, relating to trauma during the administration of the psychiatric scales. The study has a distress plan to support such patients, which entails referral to treating team if there is concern about relapse or danger to self or others. The sites have specialist psychiatric services, both inpatient and outpatient, with a team available to attend to any adverse event that may arise during the interview process.

### Methodological challenges and study limitations

Several limitations may affect the study, including that it is hospital-based, which may introduce sample bias and limit the generalisability to community samples. Another limitation is the use of tools that have limited validity in the local South African context, as they have not been used previously. Language and cultural barriers in communication will be addressed by an available isiZulu translator. A further limitation of the observational nature of the study is the attendant lack of standardisation of treatment, for which will follow the Essential Drug List (EDL) for hospital level adults (Department of Health, 2015). Although patients will follow the same algorithm, they may be maintained on different medication, depending on the individual patient treatment response. The study will, however, provide an adequate sample representing the clinical profile of patients with FEP and PLWHIV in a resource-constrained setting.

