**Figure 1 F1:**
[figure not shown]
List of all study procedures used in the patient assessment.

**Table 1 T1:** Objectives and measures used at each visit in HIV-infected and non-infected participants

Domain	Measures	Source of measures/tool	Visit 1	Visits 2 and 3	Visit 4
			Within first 6 weeks	At 3 and 6 months	At 12 months
Demographic factors	Socio-demographic data	Socio-demographic questionnaire	X		
Mental health outcome (objective 1)	Psychosis	Psychiatric history and MINI	X		
	DUP and pathways to care	WHO Encounter	X		
	Severity and nature of psychosis symptoms	PANSS	X	X	X
	Depression	PHQ9	X	X	X
	Trauma	CTQ	X		
		PCL		X	
	PTSD	Clinician-administered PTSD scale for DSM-V (CAPS 5)		X	
	Motor symptoms	ESRS	X	X	X
	HIV-associated cognitive deficit screen	CAT-Rapid and IHDS	X	X	X
	Social cognition	Neuropsychological battery		X (at 3 months only)	X
	Substance use	WHO ASSIST	X	X	X
	Quality of life	WHO-QOL BREF	X	X	X
	Biochemical haematological and radiological tests	From hospital records: full blood count, liver function test, syphilis and hepatitis test. Cerebrospinal fluid biochemistry and neuroimaging if available			
Clinical markers of HIV (objective 2)	HIV status	Confirmatory HIV ELISA			
	HIV marker	VL if HIV positive	If applicable	If applicable	If applicable
	HIV marker	CD4 if HIV positive	X		

ASSIST, Alcohol, Smoking and Substance Involvement Screening Test; CAPS, Clinician-Administered PTSD Scale; CAT, Cognitive Assessment Tool; CD, cluster of differentiation; CTQ, Childhood Trauma Questionnaire; DUP, Duration of untreated psychosis; ESRS, Extrpyramidal Symptom Rating Scale; IHDS, International HIV Dementia Scale; MINI, Mini International Neuropsychiatric Interview; PANSS, Positive and Negative Syndrome Scale; PCL, Psttraumatic Stress Disorder Checklist; PHQ, Patient Health Questionnaire; PTSD, Posttraumatic Stress Disorder; QOL BREF, Quality of Life; VL, viral load.

The cognitive battery assessment, which takes approximately 2 hours, will be administered by a clinical psychologist, at the 3-month and 12-month visits. Translation services will also be available for patients who require isiZulu translation during the interviews.

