Following collating the data for steps 1–13 in figure 1 and table 2,^22–33^ we will perform steps 14 and 15 after voluntary counselling and testing. The required HIV tests, CD4 count and viral load if HIV positive, as per the protocol, will be taken by a medical practitioner at each site. HIV testing will be carried out at baseline for all participants as well as at each visit for HIV-negative participants. A patient with a positive HIV test will be referred to the HIV clinic at the site for further management. Other investigations, such as lipid profile, which are part of routine care, will be captured from the clinical records.

**Table 2 T2:** Cognitive test battery and domains to be tested

Domains	Test
Motor skills	Grip strength^22^, Pegboard^23^
Visuospatial functioning	WAIS-R Block Design, Digit symbol^24^, and Rey-Osterrieth Rey Complex Figure (RCF)—Copy^25^
Verbal memory	Rey Auditory Verbal Learning Test (RAVLT)^26^
Non-verbal memory	RCF—Recall^25^
Problem solving/reasoning	WAIS-R Language test^24^
Language	RAVLT^26^
Word generation	Controlled Word Association Test (COWAT)^27^ Animal Naming (Letter and Category cues)^28^
Attention	WAIS-R Digit Span^24^
Executive functioning	Trail making^29^, RCF^25^, Wisconsin Card Sorting Test (WCST)^30^
Social cognition	Emotion perception (Faces Test)^31^, Theory of mind (Eyes Test)^32^, Social knowledge (Situational Feature Recognition Test) (SFRT)^33^

COWAT, Controlled Word Association Test; RAVLT, Rey Auditory Verbal Learning Test; RCF, Rey-Osterrieth Rey Complex Figure; SFRT, Situational Feature Recognition Test; WAIS, Wechsler Adult Intelligence Scale; WCST, Wisconsin Card Sorting Test.

We are keen to explore impact of pathways of care on socio-demographic and clinical variables. Rehabilitation programmes are limited as many sites lack a multidisciplinary team to support this; however, standard of care includes medication, supportive therapy, psycho-education, referral to psychology if indicated and management of comorbid substance use.

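### An as-needed isiZulu translator cannot make word-list and letter-cued scores comparable across languages, and the stated t-test has no term for language of testing

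*Protocol article*

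**What the plan says.** All references are to the protocol article.

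- **Battery.** The Methods text after Table 1 says that the cognitive battery "will be administered by a clinical psychologist, at the 3-month and 12-month visits". The next sentence reads: "Translation services will also be available for patients who require isiZulu translation during the interviews".
- **Tests.** Table 2 lists the RAVLT under verbal memory and again under language, the COWAT and Animal Naming with "Letter and Category cues" under word generation, WAIS-R Digit Span under attention, and a WAIS-R Language test under problem solving and reasoning.
- **Limitation and remedy.** Methodological challenges and study limitations concedes: "Another limitation is the use of tools that have limited validity in the local South African context, as they have not been used previously". The sentence after it gives the remedy: "Language and cultural barriers in communication will be addressed by an available isiZulu translator".
- **Analysis.** Data management and analysis compares continuous variables between two groups by an independent-samples t-test. It names no language variable.
- **Hypothesis.** The Abstract states that the HIV-positive and HIV-negative groups are expected to differ cognitively.

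**The concern.** A translator can resolve a communication problem in a clinical interview. Some tests in Table 2 are different, because the language is part of the test. Translating a word list changes the length and familiarity of the words to be recalled. Letter-cued fluency depends on how many words in the language begin with a given letter. A translated score and an untranslated one are then not the same measurement.

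Translation is offered by individual need, so the sample would contain both kinds of score. If the need for translation is more common in one HIV group, part of any difference in verbal memory, word generation or attention would reflect language of testing. If translation lowers scores and is more common among HIV-positive participants, the error points the same way as the study's own hypothesis. If language and translator use are not recorded at the visit, they cannot be reliably recovered later, and no analysis can then adjust for them.

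**Working it through.** **Inputs from the article.** The sample size is 130 per group, and the article says this allows for 10% dropout. Its inputs are an OR of 1.857 against a proportion of 0.500 (so 0.650 versus 0.500), three repeated measures, correlation 0.500, alpha 0.05 and 80% power. A two-sided two-proportion calculation gives 170 per group; times (1 + 2 × 0.5)/3 = 0.667 gives 114; divided by 0.90 gives 127, close to 130. The 130 is not disputed here. Because it already contains the dropout allowance, the analysable number is 130 × 0.90 = 117 per group.

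**Assumptions (not in the article).** Translation shifts a verbal score by s = 0.3, 0.5 or 0.8 SD. The translated share differs between HIV groups by D, from 0 to 0.30. The mean translated share is 60%.

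**Formulas.** With translated shares pA and pB:

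- Spurious mean difference = s × D.
- SD of the mixed scores = √(1 + s² × [pA(1 − pA) + pB(1 − pB)]/2).
- SE = SD × √(2/117).
- False-positive rate = P(|N(sD/SE, 1)| > 1.96).

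**One case in full: s = 0.5, D = 0.20.** pA = 0.70 and pB = 0.50, so the averaged variance term is (0.21 + 0.25)/2 = 0.23. SD = √(1 + 0.25 × 0.23) = 1.028. SE = 1.028 × 0.1307 = 0.1345. The spurious difference is 0.10 SD, so the shift is 0.10/0.1345 = 0.744, and the false-positive rate is 11.5%.

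**Range (spurious difference in SD; false-positive rate):**

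| D | s = 0.3 | s = 0.5 | s = 0.8 |
|---|---|---|---|
| 0 | 0; 5.0% | 0; 5.0% | 0; 5.0% |
| 0.10 | 0.03; 5.6% | 0.05; 6.6% | 0.08; 8.8% |
| 0.16 | 0.048; 6.5% | 0.08; 9.1% | 0.128; 15.0% |
| 0.20 | 0.06; 7.4% | 0.10; 11.5% | 0.16; 20.8% |
| 0.30 | 0.09; 10.5% | 0.15; 20.1% | 0.24; 40.5% |

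The row D = 0.16 takes the cited schooling gap (72.0% − 56.0% = 16 points) as if translator need tracked schooling completely, which is itself an assumption. The assumed mean share matters little: at 30% or 80% instead of 60%, the case s = 0.8, D = 0.20 gives 21.1% or 21.5%.

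**Equal shares (D = 0).** There is no between-group bias. The SD rises by 1% (s = 0.3) to 7% (s = 0.8), and power for a true difference of 0.4 SD falls from 86.4% to 85.7% or 81.3%.

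**The case against.** The strongest reply is that several stronger readings go beyond the text, and this is right.

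- A reader might infer that English test forms are translated live. The article states no language version for any test. Its translation offer covers interviews, and it may not extend to the psychologist-led battery. Only the position of the offer, directly after the battery sentence, supports that reading.
- A reader might infer that translated and untranslated scores are expressly pooled. That is read from a general t-test sentence that names no cognitive test.
- A reader might infer that the HIV comparison is biased. Socio-demographic profile of PLWHIV and first episode psychosis reports on sex, age and schooling, and says nothing about home language or need for translation. The KwaZulu-Natal study that "reported a higher HIV prevalence in less educated individuals" carries the article's own caveat of a small sample. The exclusion of patients with less than 7 years of schooling may narrow the gap further.

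The reply continues that language versions and covariates commonly sit in a fuller protocol or analysis plan, and that limited local validity is already declared. The first part means that silence alone is no defect. But the article goes further than silence: it names the language barrier, names a translator as the remedy and treats the matter as addressed. For word-list and letter-cued scores that remedy does not work, and declaring limited validity does not separate language from cognition in the comparison.

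The scope is limited. Grip strength, Pegboard, Block Design and the complex figure are little affected.

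**Conclusion.** The point holds in a conditional form. If the as-needed translator is used for the battery and the stated t-test is followed, the RAVLT and letter-cued comparisons, and possibly Digit Span and the WAIS-R Language test, mix language of testing with cognition. Bias in the HIV contrast further requires unequal translated shares, which the cited 16-point schooling gap makes plausible but does not show. With a 20-point difference in share and shifts of 0.3 to 0.8 SD, the false-positive rate is roughly 7% to 21%. Both the shift and the share are assumptions, and the 40.5% in the working is an extreme corner that should not be taken as the expected size. With equal shares only a modest loss of precision remains. It is worth acting on because the information has to be captured at the visit.

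**What to change.** 1. For each verbal test at 3 and 12 months, record the language of administration and whether a translator was used, and keep the language the same at both visits.
2. Compare verbal scores by HIV status in a regression with language of administration as a covariate, in place of the plain t-test.
3. Report letter-cued fluency within language, and use the category-cued (animal naming) score for the comparison that combines languages.
4. Reword the limitations section so that the translator is offered as help with communication, not as the answer to comparability of verbal test scores.

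The cost is one form field, one covariate and smaller strata for the within-language results. The covariate removes an average shift that is the same in both HIV groups; the within-language results help to judge whether that is reasonable. The 130 per group is unchanged. New isiZulu test versions are not needed for this fix: such a version would standardise delivery, but would itself need validation and would not make scores equivalent across languages.
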